## Monitoring and safety

### Audit and feedback

After each session of EAS with the family, the practitioner completes a dynamic fidelity checklist on their smartphone/tablet or computer using an online survey. The survey takes about 5–10 min to complete, depending on the number of core components and adaptations that were used in the session. After completion, an automated reminder is sent to the project coordinator, and an available interviewer calls the parent and conducts a structured telephone interview. Two additional attempts are made if the parent does not answer the call. The interviewer uses an online survey to retrieve an interview guide and plot the parent’s answers. The interview guide is based on the checklist the practitioner recently completed. That is, detailed questions are only asked about the core components that the practitioner stated were used in the last session. Additionally, parents are asked if they remember doing something else in the session. If they mention another core component, they are asked detailed questions about that as well. The interview is structured this way to limit the amount of questions asked to practitioners and parents and to prevent attrition due to long checklists and interviews. The total number of questions available to practitioners is 113; however, an average checklist requires 25–30 answers (minimum 19). An average parent interview contains 20–25 questions (minimum 14).

#### Variables audited

The variables audited are duration of session, contact since last session, adherence to core components, parents’ and children’s comprehension of core components, use of pre-defined adaptations of core components, use of additional adaptations to core components (free text), client satisfaction, client involvement in decisions, and adverse events or relevant emergent life events.

#### Feedback

Monitoring data from each site are aggregated bimonthly and used as feedback to the practitioners. [name] and TE, together with the site champions, deliver feedback on team meetings. On request from the practitioners, they can receive individual feedback to use in ongoing coaching with the site champions. Emphasis is placed on adherence to core components, frequently used adaptations, and client satisfaction. Group-level feedback reports are also delivered via newsletters.

In cases of severe drift, serious adverse events, or repeatedly poor client satisfaction, [name] and TE will confer with site champions to commence one of the following contingency plans: additional booster training with the team, individual booster training with a practitioner, or gathering of the local EAS practitioners to discuss additional adaptation or change.

### Stopping rules (discontinuation criteria)

The following criteria are considered grounds for discontinuation:If a family’s regular child welfare measure is concluded or terminated, and the family is no longer receiving child welfare supportIf the CWS practitioners or data collectors uncover acute suicidality, psychosis, abuse, or other conditions that render the EAS intervention and data collection not viable, safe, or ethicalIf the CWS practitioners uncover any serious adverse effects of the EAS intervention, rendering it unsafe to offer clientsIf the child is placed out of home and/or parents lose custody of the childWithdrawn consent from the studyWithdrawn government funding (the Research Council of Norway)Breach of ethical standards or regulations.

In cases of dropout or discontinuation, the family will be asked to complete post-assessment if it is deemed ethical and viewed as appropriate by the family’s child welfare case worker.

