#### Post-assessment

Six months after pre-assessment, the post-assessment is administered. A selection of participating families will be invited to semi-structured interviews, and a selection of participating practitioners and other stakeholders will be invited to participate in focus group interviews.

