#### Follow-up assessment

Six months after post-assessment, the follow-up assessment is administered.

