### Statistical analyses

We will consider efficacy for each of the primary outcomes. In other words, efficacy will be gauged in an outcomes-specific manner. A significance level of .05 will be used.

Outcomes will be evaluated using analysis of covariance (ANCOVA), controlling for baseline scores and covariates. Children’s age, implementation drivers, children’s mental health, social skills, and executive functions will be tested in regression models, as will possible subgroup analyses. To test for indirect effects (or mediation), models will be tested in a structural equation modeling (SEM) framework. Indirect effects variables include PASS, Five-to-Fifteen , and the end-of-intervention checklist measures. Implementation drivers as predictors of outcomes will be tested in regression models. We will evaluate effectiveness in two parts. The pre-post outcome analysis will use ANCOVA with baseline measures and covariates as control variables. We will test intervention effects including all data waves in SEM. See Figs. 2 and 3 for the theory of intervention change depicting variables included in the analyses.

We will examine and present data both in intention-to-treat (ITT) and as-treated (AT) designs, as the two approaches answer different questions. An ITT design answers the question “Does the intervention make a difference?” An AT analysis, on the other hand, answers the question “What are the effects likely to be if the client (or family) is exposed to the intervention?” We consider both of these questions important. This procedure has been recommended as best practice [46].

We will use multiple imputation for missing values for the pre-post ANCOVA in an ITT design. In the SEM models, missing data will be estimated using full information maximum likelihood.

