### Handling and follow-up of adverse events, data monitoring committee (DMC)

This study is an effectiveness trial conducted in existing child welfare agencies, not in a research facility. The intervention is considered low risk and no more intrusive than what is normally being delivered to children and families in CWS. The participating agencies have internal procedures for detecting, reporting, and following up on any adverse events in their clients. The study does not pose any restrictions on the agencies’ internal procedures for handling adverse events or offering other services if deemed appropriate. In the event of the agency terminating a family’s EAS intervention, the research team will be informed, and post-assessment will be conducted if deemed appropriate by the agency. In cases of perceived risk of adverse harm inflicted on people or property, research personnel will report to authority, abiding by law. The trial is not blinded, as the practitioners know what kind of service they offer the children and their families. No interim analyses will be conducted, in order not to bias the progression of the study. For these reasons, the current study has not appointed a DMC.

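### Outcome testing after discontinuation depends on agency judgement and names only the 6-month visit, which risks selectively missing outcome data

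*Protocol article*

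**What the plan says.** Under Stopping rules (discontinuation criteria), the protocol article lists the grounds for discontinuation. They range from acute suicidality, psychosis or abuse to an administrative event: the family's "regular child welfare measure is concluded or terminated, and the family is no longer receiving child welfare" support. One rule on outcome testing then covers all of them: "In cases of dropout or discontinuation, the family will be asked to complete post-assessment if it is deemed ethical and viewed as appropriate". The last condition reads in full "viewed as appropriate by the family’s child welfare case worker".

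The section Handling and follow-up of adverse events, data monitoring committee (DMC) takes the case in which the agency ends a family's EAS. The research team is informed and "post-assessment will be conducted if deemed appropriate by the agency".

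The visits are defined under Procedures: "Six months after pre-assessment, the post-assessment is administered", and "Six months after post-assessment, the follow-up assessment is administered". The rules for discontinued families mention the first visit and not the second.

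Statistical analyses promises intention-to-treat (ITT) results: "We will use multiple imputation for missing values for the pre-post ANCOVA in an ITT design". It also plans a structural equation model over all data waves, with full information maximum likelihood (FIML) for missing data. Randomization says that the team manager is told the allocation in order to assign the case, and that outcome assessors are blinded. The DMC section says that practitioners know which service they deliver.

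**The concern.** An ITT comparison needs outcomes sought from every randomised family in the same way, whatever happens to the support they receive. Here, whether a discontinued family is tested at 6 months turns on the view of agency staff. Those staff follow the family's course and belong to an organisation that knows the allocation and is itself delivering the service under test. Blinded assessors protect the scoring, but they have no stated say in who is scored.

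Three features make this more than ordinary caution.

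- The end of the ordinary support measure triggers the same discretion as abuse or psychosis. It may reflect how well the family is doing, and it is no safety reason to withhold a reading test, a maths test or a parent questionnaire.
- The process may differ by arm. The rule in the DMC section is worded for termination of EAS only, and one discontinuation ground (serious adverse effects of EAS) can arise only in that arm. EAS practitioners also complete a checklist after every session on comprehension, satisfaction and adverse events, so the agency holds more information on EAS families.
- The 12-month visit, which the all-waves model needs, is not named for these families.

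At stake is bias in the reading, maths and parental involvement comparisons, from data that cannot be recovered later.

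**Working it through.** **1. Does planned over-recruitment deal with this?** Inputs from Power calculation: d = 0.65, power 0.80, 39 families per group (78), 120 to be recruited. The significance level of .05 is from Statistical analyses; two-sided testing is assumed. A two-sample t-test needs 38.14 per group, which rounds up to 39 and reproduces the stated 78. Power is 0.81 with 39 per group and 0.94 with 60 per group. The tolerable loss is 1 − 78/120 = 35%. The extra families therefore protect power against substantial loss. They do nothing about which families are lost, so the issue is bias.

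**2. Size of the bias.** Let p be the proportion of an arm without an observed outcome. Let g be the gap in SD between untested and tested families that remains after covariates, taken as equal in both arms. The estimate under missing at random exceeds the true mean of an arm by p × g when the untested do worse, and falls short by the same amount when they do better. Hence

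bias in the mean difference = (difference in p between arms) × g.

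The documents give neither p nor g, so these values are assumptions:

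- 10 percentage points (6 of 60 families) and g = 0.5: 0.10 × 0.5 = 0.05 SD; 0.05/0.65 = 8% of the planned effect.
- 15 percentage points (9 of 60 families) and g = 0.8: 0.15 × 0.8 = 0.12 SD; 0.12/0.65 = 18% of the planned effect.

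The sign depends on which arm loses more families and on whether the untested do better or worse.

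**3. Simulation check.** Setting: no true effect, 60 per arm, assumed baseline–outcome correlation 0.7, loss in the EAS arm only, and ANCOVA on the observed families as a stand-in for imputation under missing at random (4,000 runs).

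| Extra loss | Residual gap | Mean estimate | Type I error |
|---|---|---|---|
| 0% | 0 | 0.00 SD | 0.050 |
| 10% | 0 | 0.00 SD | 0.052 |
| 10% | 0.5 SD | 0.05 SD | 0.071 |
| 10% | 1.0 SD | 0.10 SD | 0.118 |
| 20% | 0.5 SD | 0.10 SD | 0.105 |
| 20% | 1.0 SD | 0.20 SD | 0.309 |

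The row with 10% extra loss and no residual gap shows no bias: unequal loss alone does no harm. The other rows agree with the formula. The last row lies well beyond the range in step 2 and shows only how the problem would grow.

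**4. What the planned methods can do.** In standard form, multiple imputation and FIML assume missing at random given the data in the model. Baseline reading, maths, parental involvement, mental health, social skills and executive functioning are all collected, so loss explained by these can be handled. A decision that rests on the family's course after baseline, as seen by the agency, may not be explained by them. That remainder is g.

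**The case against.** The strongest objections mostly limit how far the point may be taken.

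- A reader might infer that discontinued families are excluded from the 12-month visit. The text does not say so. The two rules are silent on it, and the Follow-up assessment section states that visit without exceptions. In a condensed article this is an ambiguity.
- A reader might infer that the analysis ceases to be ITT. It does not: these families stay in through multiple imputation or FIML. What may be lost is their observed outcome.
- A reader might infer that the deciding case worker knows the arm. The article says this of the team manager and the practitioners. For the case worker it is an inference from the agency's role. Nor does the article say who judges whether testing is ethical.
- Some discretion is legitimate. With acute suicidality, abuse, out-of-home placement or loss of custody, a check before a home visit is reasonable, and testing cannot be required once consent is withdrawn. The complaint that the ground is no reason to stop measuring fits the end of ordinary support best.
- The loss rates and gaps are assumed, and a gap that remains after baseline adjustment can be smaller than a raw one. The resulting bias is moderate.
- A sensitivity analysis for data missing not at random may be in an analysis plan that is not shown, so its absence is not counted here.

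All of this stands. It leaves the core in place: a stated rule makes outcome collection after discontinuation depend on agency judgement, whatever the ground, and names one visit of two.

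**Conclusion.** The point holds as a risk created by a stated rule. It is not a demonstrated loss of validity. Following the rule can leave outcomes missing for reasons tied to the family's course, possibly at different rates by arm, and the planned missing-data methods would correct this only as far as observed data explain it. Under the assumed 10 to 15 percentage point difference in loss and 0.5 to 0.8 SD residual gap, the bias is about 0.05 to 0.12 SD, or 8% to 18% of d = 0.65, in either direction. With equal loss and equal gaps in both arms, or no residual gap, it is zero. The documents do not support a claim that selective loss will occur, or in which direction. Because the number of affected families is unknown and the bias in this range is moderate, this is a should-fix. Recruitment has begun, and outcomes not collected at 6 and 12 months cannot be obtained afterwards.

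**What to change.** Amend the two passages on testing after discontinuation so that stopping EAS or ordinary support is kept separate from leaving the study:

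1. The research coordinator invites every randomised family, in both arms, to both the 6-month and the 12-month assessment, whether or not EAS or the support measure has ended.
2. The exceptions are withdrawn consent, or a safety, ethical or legal reason that the agency documents.
3. Each withheld assessment is logged with its reason and by arm, so that the extent and balance of the loss can be reported.

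This concerns data collection only. The discontinuation grounds and the agencies' own safety procedures stay as they are. The cost is a short amendment, some coordinator time and a few more home visits of a kind already planned.

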### Data management

The Regional Centre for Child and Adolescent Mental Health, Eastern and Southern Norway has a license and data management agreement with Confirmit. All electronic data are collected using the web-based tool Confirmit Authoring, and all websites used to collect data are encrypted with a security clearance. Data on paper are stored in a secure safe with access restricted to authorized research personnel. All data are stored in accordance with standards and regulations set by the ethics committee Norwegian Centre for Research Data (NSD). Sensitive information is stored separately from directly identifiable information. An identification key is stored electronically in a secure database. Only authorized research personnel have access to the key. Further information can be provided upon request.

### Handling and follow-up of adverse events, data monitoring committee (DMC)

This study is an effectiveness trial conducted in existing child welfare agencies, not in a research facility. The intervention is considered low risk and no more intrusive than what is normally being delivered to children and families in CWS. The participating agencies have internal procedures for detecting, reporting, and following up on any adverse events in their clients. The study does not pose any restrictions on the agencies’ internal procedures for handling adverse events or offering other services if deemed appropriate. In the event of the agency terminating a family’s EAS intervention, the research team will be informed, and post-assessment will be conducted if deemed appropriate by the agency. In cases of perceived risk of adverse harm inflicted on people or property, research personnel will report to authority, abiding by law. The trial is not blinded, as the practitioners know what kind of service they offer the children and their families. No interim analyses will be conducted, in order not to bias the progression of the study. For these reasons, the current study has not appointed a DMC.

### Access to source data

The Regional Centre for Child and Adolescent Mental Health ensures that the investigator/institution will permit trial-related monitoring, audits, reviews, and regulatory inspections, by providing direct access to source data/documents if needed, and that such inspections do not violate the rights and/or anonymity of trial participants, including children, their families, their therapists, or other CWS employees.

## Discussion

This hybrid study has two main aims: (1) to evaluate the feasibility of an Integrated Knowledge Translation (IKT-K) model used in Child Welfare Services (CWS) designed to develop, implement, and evaluate empirically supported practice; and (2) to test the effectiveness of Enhanced Academic Support (EAS), a home-based intervention to improve academic achievement in children and their families in child welfare.

Advances in implementation science have outlined strategies that are likely to be pivotal to succeed in translational efforts, such as developing collaborative partnerships with stakeholders, using facilitation, and adapting and tailoring to context [47]. Similar strategies have long been used in the field of quality improvement, such as co-creation (or co-production) methods [48], often combined with iterative process models designed for continuous improvement [49]. The IKT-K model applied in this study attempts to utilize the best available evidence from implementation science together with established quality improvement methods to advance knowledge translational efforts. Involving stakeholders in mutually dependent partnerships is an integral strategy in this study, operationalized using facilitated co-creation approaches to locally tailor adaptable aspects of the study. The aim of these strategies is to utilize local knowledge and expertise, ensure buy-in from stakeholders, and thus promote acceptability, implementation, and sustainment of the newly introduced practice change. If feasible, this model can offer a pragmatic, efficient, and usable approach to development, implementation, and sustainment of evidence-based practice, which in turn can support knowledge translation and quality improvement in health, care, and welfare services.

Providing effective academic support to children in CWS can be of great value to both individual families and society at large. The need for academic support in child welfare populations is extensive, and CWS agencies are required to contribute to helping these children academically. However, these agencies are not provided with additional resources to deliver academic support to the families they serve. Hence, they need means to deliver academic support that fits within their current practice. EAS is a pragmatic intervention tailored to child welfare daily practice by the CWS agencies using it. Building the intervention around core components offers a much-needed flexibility that enables child welfare practitioner to incorporate empirically supported academic support within their existing practice. EAS requires limited training and resources and, if effective, could prove a highly cost-effective intervention given the large returns successful investments in education can provide for individuals and society.

### Trial status

Recruitment commenced in January 2018, and the trial is currently in progress. The estimated completion date of the trial is December 2019.

## Abbreviations

BAU: Business as usual
CWS: Child Welfare Services
EAS: Enhanced Academic Support
EBP: Evidence-based practice
ICS: Implementation Climate Scale
IKT: Integrated Knowledge Translation
IKT-K: Integrated Knowledge Translation-KOBA model
KOBA: Kunnskapsoverføring i Barnevernet
PASS: Parent and School Survey
SDQ: Strengths and Difficulties Questionnaire
SSRS: Social Skills Rating System
